## Abstract

**Background:**

Diarrhea-predominant irritable bowel syndrome (IBS-D) is the most common subtype of IBS. Acupuncture is commonly used to treat IBS-D, but its effect is uncertain because of the poor quality of prior studies. This trial aims to evaluate the efficacy and safety of acupuncture treatment for IBS-D through comparisons with sham acupuncture.

**Methods/design:**

This is a large-scale, multi-center, randomized, two-arm interventional clinical trial. Participants will take part in a total of 20 weeks of study, which contained 3 phases: 2-week screening, 6-week treatment, and 12-week follow-up. Based on the composite response rate of the primary endpoint in our pilot study (a sham acupuncture response rate of 27% and a true acupuncture of approximately 45%), 280 randomly allocated participants were planned. Eligible participants will be randomly assigned to the true acupuncture group and sham acupuncture group according to a ratio of 1:1, and a total of 15 sessions of treatment overall 6-week treatment period will be brought. The primary endpoint is a composite response rate at week 6, and the responder is defined as who responses in both abdominal pain intensity and stool consistency. Furthermore, composite response rates at other weeks, IBS Symptom Severity Scale, IBS Quality of Life, Adequate Relief scale, and individual IBS symptoms (abdominal pain, bloating, stool frequency) are chosen as secondary endpoints.

**Discussion:**

This trial may provide high-quality evidence for the efficacy and safety of acupuncture in the treatment of IBS-D. The results of this study will be published in peer-reviewed journals.

**Trial registration:**

Chinese Clinical Trial Registry: ChiCTR2100044762. Registered on 26 March 2021.

## Background

Irritable bowel syndrome (IBS) is a globally prevalent disorder characterized by persistent or intermittent abdominal pain, bloating, changes in stool form and frequency, and defecation habits. Although IBS is non-fatal, the symptoms impair quality of life and social functioning, which lead to a healthcare burden. The annual direct and indirect costs associated with IBS are estimated to be up to billions or more in several countries [1–3]. In the absence of distinct biomarkers, IBS is typically diagnosed according to the patients’ self-reported symptoms, such as the Rome IV or Rome III criteria. According to a systematic review and meta-analysis on the global prevalence of IBS in 2020 [4], diarrhea-predominant IBS (IBS-D) is the most common subtype when the Rome IV criteria were applied. Routine clinical treatments for it tend to improve the most troublesome symptoms, such as abdominal pain and bowel habit. Among them, antidiarrheals and antispasmodics were used as first-line therapies for predominant stool pattern improvement in IBS, but most randomized controlled trials of these drugs are outdated and hampered by suboptimal methodology and heterogeneous patient selection, and the occurrence of side effects and adverse events greatly reduced the therapeutic effect and patients’ satisfaction, which resulted in a higher demand for alternative therapies [5].

Acupuncture is considered as a beneficial alternative treatment for functional gastrointestinal disorders [6]. Although whether acupuncture is an alternative treatment for IBS still remains controversial [7–11], previous studies have shown that acupuncture may affect IBS from the perspectives of the brain-gut axis, gastrointestinal motility, and visceral hypersensitivity [12, 13]. Furthermore, the recent clinical randomized trial supported that acupuncture may be more effective than pinaverium bromide for the treatment of IBS-D, with effects lasting up to 12 weeks [14]. Regrettably, the efficacy endpoints of most clinical trials of acupuncture for IBS often do not meet the current recommendations from the US Food and Drug Administration (FDA) or the European Medicines Agency. We have conducted a pilot clinical randomized trial with a minimum sample size (*n* = 90) in 2020 using efficacy endpoints that meet the current recommendations from the FDA [15]. For the primary endpoint, the composite response rates at week 4 between true acupuncture (specific acupoints and non-specific acupoints) and sham acupuncture (non-acupoints) were 46.67% and 26.67%, respectively, and the line charts trends of all endpoints of specific acupoints acupuncture are consistent and better than sham acupuncture. However, the effective response rates of different acupuncture groups and sham acupuncture group have no statistical significance, and we considered that the insufficient sample size cannot be ignored. Therefore, a large-sample, multicenter randomized controlled trial with high methodologic quality was considered necessary.

Accordingly, we designed the large-scale trial in order to provide substantive evidence on acupuncture as a reliable option. The primary objective is to evaluate the efficacy of acupuncture for the treatment of IBS, and the second objective is to assess the safety of the present acupuncture protocol.

## Methods/design

### Trial design

This is a large-scale, multi-center, randomized, two-arm interventional clinical trial (Fig. 1). Participants will take part in the 20 weeks study which included 3 phases: 2-week screening (weeks − 2, − 1), 6-week treatment (weeks 1–6), and 12-week follow-up (weeks 7–18). Participants will be recruited in 6 grade III level A hospitals in China: (I) the Affiliated Hospital of Hebei University of Chinese Medicine, (II) the Teaching Hospital of Chengdu University of Traditional Chinese Medicine, (III) the Affiliated Hospital of Shandong University of Traditional Chinese Medicine, (IV) the First Teaching Hospital of Tianjin University of Traditional Chinese Medicine, (V) the Dongfang Hospital Beijing University of Chinese Medicine, and (VI) Shaanxi Provincial Hospital of Chinese Medicine. The study protocol was approved by the Medical Ethics Committee of Beijing University of Chinese before the study started. All personnel participating in this trial will be uniformly trained on the content of the trial.

**Fig. 1 Fig1:**
[figure not shown]
The flow diagram of this trial

### Participants

Participants will be recruited by the clinical recruiters using advertisements (e.g., flyers in physician offices, articles on WeChat official accounts). Data of the trial will be collected by the REDCap electronic data capture (EDC) system [16]. Every participant will sign an informed consent form before randomization. Patients will be considered to have dropped out if they did not complete 80% of the total treatment sessions.

#### Inclusion criteria

The following are the inclusion criteria:

(I)Aged between 18 and 75 years (either sex)(II)Fulfilled Rome IV diagnostic criteria for IBS-D(III)Type 6 or 7 of the Bristol Stool Form Scale appeared for at least 4 days and type 1 or 2 appeared for less than 4 days in the last 2 weeks; the average score of daily abdominal pain was ≥ 3 in the last week(IV)No treatment of acupuncture in the last 6 months(V)No use of antidepressant or IBS medication within 2 weeks before treatment, including traditional Chinese medicine (TCM) or proprietary Chinese medicine, antidiarrheal, antispasmodic, intestinal antibiotics, probiotics, and so on

#### Exclusion criteria

The following are the exclusion criteria:(I)Participants with inflammatory bowel disease, microscopic colitis, celiac disease, Crohn’s disease, and other organic bowel diseases (age ≥ 50 years or have the following alarm signs that will be required to provide colonoscopy report within nearly 2 years: unexplained weight loss (weight loss > 10% within 3 months), hematochezia caused by non-hemorrhoids or anal fissure, nocturnal diarrhea, family history of colorectal cancer)(II)Diabetes mellitus and abnormal thyroid function(III)Severe acute or chronic organic diseases and kidney or liver diseases(IV)History of previous abdominal surgery (appendectomy, hemorrhoidectomy, or polypectomy greater than 3 months post-surgery is allowed)(V)Pregnancy or lactation(VI)History of alcohol and drug abuse(VII)Participate in other clinical trials

### Interventions

The true acupuncture (TA) group and sham acupuncture (SA) group will be set in this trial. The acupuncturists will be required to have a minimum licensed time of 3 years. Participants will receive 15 sessions of treatment overall 6-week treatment duration. Treatment will be given 3 times a week for the first 3 weeks (once every other day) and 2 times a week for the last 3 weeks (once every three days). Single-use sterile needles (0.30 mm in diameter and 40 mm in length or 0.30 mm in diameter and 25 mm in length; Hwato, Suzhou, China) will be used in the TA group. Blunt-tipped placebo needles will be used (similar to the Streitberger design) in the SA group which can provide participant-blinding effects with a similar appearance to conventional needles but no skin penetration [17, 18]. Adhesive pads will be placed on puncture points in both groups. The use of blunt-tipped placebo needles and adhesive pads is to help maximize the blinding of participants in the SA group, and adhesive pads also have the function of fixing blunt-tipped placebo needles. The research manual will be developed prior to the trial, and uniform training will be provided to all study staff (including acupuncturists), in areas such as recruitment, evaluation of outcomes, positioning of acupuncture acupoints, and acupuncture manipulation. During the treatment phase, each sub-center will have 1–2 acupuncturists implementing both groups of the intervention. We will require the acupuncturist to be responsible for the complete treatment of each patient rather than requiring the acupuncturist to specialize in a particular group of treatments, so that patients will not be able to differentiate between the treatment groups through the acupuncturist. In addition, patients assigned to the placebo group will be offered a free acupuncture treatment at the end of the follow-up period if they wish.

### TA group

Five fixed acupoints and one of three optional acupoints will be chosen for the treatment of participants in the TA group (Table 1). Based on the specific acupuncture acupoint combinations theory of TCM in *Lingshu* [19], the acupuncture prescription was developed by reviewing the frequency of acupuncture points in the relevant literature and combining it with the opinions of acupuncturists. The different types of TCM syndrome further guide the selection of optional acupuncture acupoints, such as Taichong (LR3) for the syndrome of liver depression and spleen deficiency, Sanyinjiao (SP6) for the syndrome of spleen deficiency and dampness obstruction, and Neiting (ST44) for the syndrome of spleen-stomach damp-heat. At the first visit, the acupuncturist will diagnose the patient’s TCM syndrome through questioning, tongue examination, and pulse and then select the appropriate optional acupoint. After sterilization, the acupuncturist will insert single-use sterile needles into the deep tissue layers through adhesive pads of acupoints. Following needle insertion, small, equal manipulations of twirling, lifting, and thrusting will be performed on all needles to reach *deqi* (a component sensation, including soreness, numbness, distension, and heaviness). The retention time of single-use sterile needles will be 30 min, during which the operation of *deqi* will also be performed every 10 min during the needle retention period.

**Table 1 Tab1:** Locations of acupoints for the TA group

	Acupoint	Location
Fixed acupoints of the TA group	*Tianshu* (ST25)	On the horizontal line of the navel, 2 cun^a^ beside the anterior midline
	*Zhongwan* (RN12)	On the anterior midline of the upper abdomen, 4 cun superior to the navel
	*Guanyuan* (CV4)	On the anterior midline of the abdomen, 3 cun inferior to the navel
	*Zusanli* (ST36)	3 cun directly below ST35 and one fingerbreadth lateral to the anterior border of the tibia
	*Shangjuxu* (ST37)	On the anterolateral aspect of the leg, 6 cun inferior to the ST35, and one fingerbreadth lateral to the anterior border of the tibia
Optional acupoints of the TA group	*Taichong* (LR3)	In the depression anterior to the junction of the first and second metatarsal bones
	*Sanyinjiao* (SP6)	On the tibial aspect of the leg, posterior to the medial border of the tibia, and 3 cun superior to the prominence of the medial malleolus
	*Neiting* (ST44)	On the instep, between the second and third toes of the red and white flesh behind the webbed margin

^a^1 cun (≈ 20 mm) is defined as the width of the interphalangeal joint of the participant’s thumb

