### SA group

The positioning of non-acupoints adheres to the following two principles: first, the sites of non-acupoints are selected away from the meridians or conventional acupoints; second, the distribution areas of non-acupoints are similar to that of the acupuncture acupoints to avoid patients differentiating groups by the location of acupoints. Five non-acupoints will be selected for the treatment of the SA group (Table 2). Unlike the TA group, the SA group will not perform manual operations for needles after needle insertion and pretend to perform the manual operation of *deqi* every 10 minutes during needle retention time.

**Table 2 Tab2:** Locations of non-acupoints for the SA group

Non-acupoint	Location
Non-acupoint 1	On the abdomen, 2 cun^a^ superior to anterior superior iliac spine, between the gallbladder meridian and the spleen meridian
Non-acupoint 2	On the abdomen, 2 cun inferior to the navel, 1 cun beside the anterior midline, between the kidney meridian and the stomach meridian
Non-acupoint 3	On the lateral aspect of the leg, 3 cun inferior to GB34, between gallbladder meridian and bladder meridian
Non-acupoint 4	On the leg, 2 cun superior to the medial malleolus, in the middle of the medial tibia, between the liver meridian and the spleen meridian
Non-acupoint 5	On the leg, the midpoint of the line between GB40 and ST41, between the gallbladder meridian and the stomach meridian

^a^1 cun (≈ 20 mm) is defined as the width of the interphalangeal joint of the participant’s thumb

All participants will be advised to keep their routine diets and lifestyles during the study procedure. Loperamide (Imodium, Xian Janssen Pharmaceutical Ltd., China), will be used as a rescue medication under the guidance of gastroenterologists whenever necessary. The medication status and other non-irritable bowel syndrome drug applications of participants will be strictly recorded during the trial.

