### Randomization, sequence generation, and blinding

Eligible participants will be randomly assigned to the TA group and SA group according to the ratio of 1:1 by central stratified block randomization in the REDCap EDC system with a dynamic block size. The randomization sequence was created by a biostatistician who did not participate in this trial. Recruiters will be responsible for registering the participants, and acupuncturists will assign the participants to the intervention. The different REDCap EDC system permissions depend on the role of the personnel. Only the acupuncturist and his or her assistant can obtain the randomization grouping information. The clinical recruiters, outcome assessors, data managers, and statisticians will be blinded to the group allocation.

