For blinding assessment, all participants will be asked to guess which treatment they received at the end of the last treatment in week 6. Additionally, the Credibility/Expectancy Questionnaire within 5 min will be used to evaluate the credibility and expectancy of participants after the first treatment [23]. The schedule of enrollment, intervention, and assessments is shown in Fig. 2. The incidence of AEs and any use of loperamide will be recorded at 6-week treatment and 12-week follow-up.

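### The individual TCM diagnosis is described only in the true-acupuncture procedure, with no matching real or simulated consultation in the sham procedure

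*Protocol article*

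**What the plan says.** All references are to the protocol article.

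- **TA group.** "Five fixed acupoints and one of three optional acupoints will be chosen for the treatment of participants in the TA group". The optional point follows from a diagnosis that the acupuncturist makes at the first visit, establishing the "TCM syndrome through questioning, tongue examination, and pulse and then select the appropriate optional acupoint". The text then moves directly to sterilisation and needle insertion.
- **SA group.** "Five non-acupoints will be selected for the treatment of the SA group". There is no optional point and no diagnostic step. The one contrast the section draws with TA concerns manipulation: "Unlike the TA group, the SA group will not perform manual operations for needles after needle insertion and pretend to perform the manual operation".
- **Interventions.** The two arms share adhesive pads and needles of similar appearance, and "each sub-center will have 1–2 acupuncturists implementing both groups of the intervention". A research manual and uniform staff training are mentioned but not shown.
- **Randomization, sequence generation, and blinding.** "Only the acupuncturist and his or her assistant can obtain the randomization grouping information".
- **Outcomes and follow-up.** The Credibility/Expectancy Questionnaire "will be used to evaluate the credibility and expectancy of participants after the first treatment", and participants guess their group after the last treatment in week 6.
- **Discussion (limitations).** Unblinded acupuncturists and a residual placebo effect are acknowledged. Unequal consultation is not mentioned.

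**The concern.** A sham control isolates needling only if everything else the participant experiences is the same in both arms. Being questioned, having tongue and pulse examined, and then receiving a point chosen for one's own syndrome is visible, personal attention. It can raise expectancy. In the text this attention belongs to TA alone, and it comes from a practitioner who can know the allocation.

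The primary endpoint combines a pain score with days of loose stool, both of which depend on what the participant reports. The Discussion itself says that expectation and blinding appear to influence acupuncture effects. If only TA participants had the consultation, part of any TA–SA difference could come from contact rather than needling, and the planned chi-square comparison could not separate the two.

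**Working it through.** **1. Comparing the two procedures**

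| Element | TA | SA | Matched in the text? |
|---|---|---|---|
| Needle appearance, pads | Conventional needle, pad | Blunt placebo needle of similar appearance, pad | Yes |
| Practitioner | 1–2 per sub-center | The same people | Yes |
| Body regions | Abdomen and leg/foot | Similar areas by design | Yes |
| Manipulation every 10 min | Performed | Pretended | Yes, by simulation |
| Individual TCM diagnosis | Questioning, tongue, pulse | Not described | No |
| Individually chosen point | One of three | None | No |

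The diagnosis has one stated purpose, choosing the optional point, and that choice exists only in TA. A site reading the SA section has no stated reason to carry it out there.

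**2. The plan's own sample size**

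Inputs from the Sample size section: 27% versus 45%, 80% power. Alpha of 0.05 is from Statistical analyses; two-sided testing is assumed. The mean rate is (0.27 + 0.45)/2 = 0.36.

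n per arm = [1.960·√(2·0.36·0.64) + 0.842·√(0.45·0.55 + 0.27·0.73)]² / 0.18²

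= (1.330 + 0.561)² / 0.0324 ≈ 110.4, rounded up to 111 per arm, or 222 in total.

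Allowing for 20% dropout, 222/0.8 = 277.5, so 278, and the plan uses 280. These figures reproduce and are not disputed.

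**3. Illustration of what unequal contact could do**

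The documents give no contact effect, so its size is an assumption, varied here from 1 to 5 points. Suppose needling has no effect, SA responds at 27%, and contact alone adds b points in TA. The probability that the two-sided Pearson chi-square test (no continuity correction) gives P < 0.05 is the sum, over all pairs of responder counts that reject, of Bin(x; n, 0.27 + b) × Bin(y; n, 0.27).

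| Assumed b | 111 per arm | 140 per arm | b as share of the planned 18 points |
|---|---|---|---|
| 0 | 5.0% | 5.1% | 0 |
| 1 point | 5.3% | 5.5% | 1/18 = 6% |
| 3 points | 7.8% | 8.7% | 3/18 = 17% |
| 5 points | 12.9% | 15.2% | 5/18 = 28% |

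At 1 point the inflation is negligible. At 5 points the false-positive rate is between two and a half and three times nominal. It rises with sample size, because a larger trial detects the same bias more readily.

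**The case against.** The strongest reply is that silence is not absence. The SA section is short and does not restate shared steps: it repeats neither the 30-minute retention time nor sterilisation, and its one explicit contrast concerns manipulation. The consultation might be given to everyone and be set out in the research manual, which is not shown. This part stands. A reader might infer that SA participants definitely receive no consultation; the article does not say so.

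Two further inferences are tempting and also unsupported. One is that the diagnosis happens after allocation is known. The text says only that it takes place at the first visit, which is not dated against randomisation, and there is a 2-week screening phase beforehand. The other is that it falls just before credibility and expectancy are rated. That requires the first visit and the first treatment to be the same occasion, which the article never states. Nor is it a defect in the analysis that syndrome type might be unrecorded in SA, since no stated analysis uses it.

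It can also be said that the trial measures expectancy and tests blinding, uses the same acupuncturists in both arms, and admits that they are unblinded. Those are real strengths. However, measuring expectancy or listing a limitation can reveal an imbalance without removing it, and sharing practitioners does not equalise what they do at the first visit. Finally, nothing in the documents shows that first-visit contact would still affect response at week 6, so a contact effect near zero is possible.

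What remains is that an article which specifies its matching in detail leaves this visible element unmatched.

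**Conclusion.** The point holds in a limited form. The TCM diagnosis is described only within the TA procedure, is done by a practitioner with access to the allocation, and has no described counterpart in SA. Followed as written, this would add individualised contact in one arm of a sham comparison and could bias participant-reported outcomes towards TA. Whether the arms differ in practice cannot be settled from the article.

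The size is unknown. A false-positive rate of about 5–13% (111 per arm) or 5–15% (140 per arm) rests wholly on an assumed 1 to 5 point contact effect, a 27% sham rate and no needling effect. It is an illustration of sensitivity, not an estimate of bias in this trial. The sample size is unaffected. The change is worth making because it is cheap and is needed under either reading: if both arms are already examined alike, the text should say so.

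**What to change.** State that the same TCM examination (questioning, tongue, pulse) is done for every participant before randomisation, that the syndrome is recorded in REDCap, and that the record is used to choose the optional point only in those allocated to TA. Neither set of needling points changes.

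The cost is a few minutes per SA participant and one eCRF field. If the examination is already done in both arms before allocation, only a sentence is needed.

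The trial is already recruiting. If SA participants have not been examined so far, the change alters the SA procedure part-way through and leaves two SA cohorts. For participants already enrolled, record whether and when the examination was done, and report this by arm so that readers can judge any imbalance.
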